## 8. STUDY INTERVENTION

### 8.1 Identity of Investigational Products

#### 8.1.1 Experimental Intervention

In this study, the IMP is tirzepatide (*Mounjaro*®). This medication has marketing authorization in Switzerland. Tirzepatide (*Mounjaro*®) is a dual glucose-dependent insulinotropic polypeptide (GIP) receptor and glucagon-like peptide-1 (GLP-1) receptor agonist.

The recommended starting dosage is 2.5 mg injected SC once weekly. After four weeks, the dose could be increased to 5 mg injected SC once weekly until an upper limit dosage of 15 mg SC once weekly (in 2.5 mg increments after at least four weeks on the current dose) (53). For this study, the target dose is 5 mg, which is the minimum approved dose for glucose control.

#### 8.1.2 Control Intervention (standard/routine/comparator treatment)

The participants in the control group will be requested to continue to use their (automated) insulin-related standard of care (SoC) and concomitant medication (if it does not represent an exclusion criterion).

#### 8.1.3 Packaging, Labelling, and Supply (re-supply)

The IMP (tirzepatide) will be administered in its primary package. Tirzepatide (*Mounjaro*®) is a clear, colorless to slightly yellow solution available in cartons containing four pre-filled single-dose vials as follows: 2.5 mg, 5 mg, 7.5 mg, 10 mg, 12.5 mg, or 15 mg per 0.5 mL in a single-dose pen or single-dose vial.

Tirzepatide will be labeled in all required local languages according to annex 13 from Eudralex-Good Manufacturing Practice (GMP). Labeling will be performed by authorized personnel.

Participants will be provided with insulated bags containing cooling gel packs to transport the tirzepatide from the site to home.

The study team will have a stock of tirzepatide (for supply and re-supply) at the clinical recruitment site (See Subsection 8.1.4).

#### 8.1.4 Storage Conditions

Tirzepatide (*Mounjaro*®) will be stored in a secure refrigerator at 2°C to 8°C (36°F to 46°F) at the study site and in the original carton to protect from light. The temperature log will be monitored at the site, and any temperature fluctuation will be reported as a deviation (in this case, the IMP is not given to the participant and is kept until destruction). If needed, each single-dose pen or vial can be stored unrefrigerated at temperatures not exceeding 30°C (86°F) for up to 21 days. Tirzepatide should not be frozen or used if it is frozen.

The principal investigator and the study team will be responsible for confirming that appropriate temperature conditions have been maintained during transit for all study treatments received and that any discrepancies are reported and resolved before using the study treatment. All the provided treatments will be stored in a secure (locked), environmentally controlled, and monitored (manual or automated) place following the labeled storage conditions per the manufacturer. Access will be limited to the investigators and authorized study members. All the participants will be instructed about the storage and handling conditions to be fulfilled at their place. Refer to the Swiss product information for detailed information on the handling and safety of *Mounjaro*® (9)

### 8.2 Administration of experimental and control interventions

#### 8.2.1 Experimental Intervention

The IMP (tirzepatide) is administered weekly by the participant at any time of the day, with or without meals. It should be injected subcutaneously in the abdomen, thigh, or upper arm, rotating the injection sites for each dose. A maximum dose of 5 mg SC weekly will be administered as a treatment dose (after the titration phase with 2.5 mg SC/week), and all participants will receive verbal and written education on tirzepatide pen use(53).

#### 8.2.2 Control Intervention

The control intervention consists of the (automated) insulin-related SoC and concomitant medication (if it does not represent an exclusion criterion). Participants in the control group will continue with their

home treatment according to international guidelines and the criteria of their treating physician(14).

### 8.3 Dose modifications

In this study, participants will start with an initiation dose of 2.5 mg weekly, and after four weeks, they will receive a stable dose of 5 mg weekly. In case of intolerance to the medication, the dose can be scaled back. However, the tirzepatide dose escalation scheme has been designed to minimize the development of GI symptoms. During the dose escalation period, every effort should be made by the investigator to escalate and maintain participants on the corresponding tirzepatide dosage (maximally 5mg/week). After the stabilization, the dose modification for tirzepatide is not permitted. **See Annex 8** for the plan to mitigate gastrointestinal symptoms.

If a dose is missed, the participant will be instructed to administer tirzepatide as soon as possible, within four days (96 hours) after the missed dose. If more than four days have passed, the missed dose should be skipped, and the next dose should be administered on the regularly scheduled day. The day of weekly administration can be changed (if necessary) if the time between the two doses is at least three days (72 hours).

### 8.4 Compliance with Study Intervention

The IMP compliance will be determined by the following:

- IMP administration data will be recorded by the participant weekly in a logbook and reviewed by the investigator at each on-site study visit while the participant is still present. If necessary, the participant should be asked to fill in any missing answers.
- If a dose is missed, the missed dose will be recorded as “not taken.” A participant will be considered non-compliant if he or she is judged by the investigator to have intentionally or repeatedly taken less than the prescribed amount of medication.
- In addition to the assessment of a participant’s compliance with the IMP administration, other aspects of compliance with the study procedures will be assessed at each visit based on the patient’s adherence to the visit schedule, completion of the medication logbook, and any other parameters the investigator considers necessary.

Participants considered to be poorly compliant with their medication and/or the study procedures will receive additional training and instruction as required. They will be reminded of the importance of compliance. At the end of the study, treatment compliance will be defined as taking at least 75% of the required doses of the study drug.

### 8.5 Data Collection and Follow-up for Withdrawn Participants

The medical follow-up of prematurely withdrawn or dropped-out participants from the investigation is described in **Subsections 9.2.5 and 9.2.6**.

### 8.6 Trial-specific Preventive Measures

A serum pregnancy (serum beta-Hcg) test will be performed for all female participants of childbearing potential at the screening visit as part of the eligibility assessment. The result must be available before randomization and the first injection of the study drug. Additional pregnancy in urine tests will be repeated during the study.

If pregnancy occurs after inclusion and during the ongoing study, it will be reported to the Sponsor within a maximum of 24 hours. Consequently, the pregnant participant will be withdrawn from the study (**See Annex 7**).

In addition, the study team will encourage the participants to obtain glucagon Intranasal (*BAQSIMI*®) or vial injection (*GlucaGen*® *HypoKit*®) through prescription. All participants must have glucagon products as part of the standard of diabetes care. The participant and their caregiver (if any) must be trained on using glucagon products (**See Annex 4**, hypoglycemia risk mitigation plan).

The study participants will receive a ketone meter (**See Annex 5** for Guidance on checking for ketones).

The use of any rescue medication and concomitant medications will be recorded in the eCRFs.

### 8.7 Concomitant Interventions (treatments)

**Section 7.1** describes the medications not allowed before and/or during the study. **Section 8.6** and **Annex 4** describe rescue treatments and relevant interventions for hypoglycemia. Participants will be encouraged to continue their chronic treatment and medications if these do not fall within the exclusion

criteria. Concomitant medications will be recorded in the eCRFs.

## 8.8 Study Drug Accountability

Only the study team can provide the IMP (tirzepatide). Study staff will regularly assess whether the patient is correctly administering the IMP and storing it according to the provided instructions.

The study site must report the dispensing and return of the IMP (including the unique patient number [UPN], date, vials dispensed/returned, and batch number) on an IMP accountability log. The study's site clinical coordinator will sign this log, which is stored in the investigator's site file (ISF) and checked by the clinical research associate (CRA).

## 8.9 Return or Destruction of Study Drug

Participants will be instructed to dispose of the pens in their original boxes (as there is no risk of puncture) and return all used pens and boxes to the study center during their next on-site visit. The returned used pens will be reconciled with the information recorded in the participant's logbook for IMP accountability and compliance evaluation. At the study site, all used pens will be safely disposed of per local regulations.

Unused or partly unused investigation product must be checked and reconciled with the participant's logbook. Unused, partly unused, or expired investigation products must be destroyed at the site according to local guidelines but only after the inspection of the CRA and receipt of instructions from the Sponsor. The destruction should be documented using the IMP accountability log.

## 8.10 Study accessories

### 8.10.1 CGM system

The Dexcom G7 CGM system, Dexcom Suisse GmbH, [name], Switzerland (CE Cert. No: CE 591560), is a commercially available device that will be used in the study to collect CGM values. The sensor and transmitter are integrated in this model.

Data from a Dexcom G7 CGM system will be collected and used as the reference for blood glucose levels. The Dexcom G7 CGM system is a CE-marked device indicated for the management of diabetes mellitus in people aged two years and older. To standardize and harmonize glucose data collection independently of the AID system, all participants will be provided with study CGMs (Dexcom G7). Participants must wear the Dexcom G7 sensor in addition to their existing sensor connected to the AID system (unless Dexcom G7). Data from the study sensor will not be blinded and will be used solely for research purposes. The CGM sensor should be replaced at least once every ten days. The investigator will provide the necessary sensors (for re-supply) at visits 2 and 3.

Coded data (i.e., not containing identifiable patient information) from the CGM and AID system will be continuously or intermittently uploaded to a cloud-based platform accessible only to study team members.

The (study) CGM values are for monitoring only and should not be used for diabetes management during the study.

### 8.10.2 Ketone and Glucose Meter

The Abbott FreeStyle Optimum Ketone monitoring system is intended for in vitro diagnostic use for the quantitative measurement of  $\beta$ -ketone ( $\beta$ -hydroxybutyrate) in fresh capillary whole blood samples. The meter uses single-use test strips to measure the concentration of  $\beta$ -ketones in fresh capillary and venous whole blood samples. Blood ketone strips measure  $\beta$ -Hydroxybutyrate are considered as 'Gold Standard' in the management of Diabetic Ketoacidosis. The necessary Ketone meters (and corresponding material (test strips, lancing device, and lancets) will be provided (free of charge) by the investigator at visits 2 and 3.

The participant also can use the same device to self-monitoring blood glucose (SMBG) according to the medical routine. The SMBG is a routine process part of the SoC. These values are used to verify the measured CGM data and to calibrate the CGM sensor if necessary.

### 8.10.3 Physical activity trackers

The Fitbit sense 2, Fitbit LLC, [name] USA is a commercially available device that will be used in the study to collect activity data. The Fitbit sense 2

uses state-of-the-art technology to track sleep and heart monitoring. Patients will be equipped with a Fitbit sense 2 at visit 1 and will wear the device throughout the study. The Fitbit sense 2 is used to collect additional physiological data:

- Heart rate and heart-rate variability
- Oxygen saturation
- Respiration rate
- Stress level
- Sleep stages
- Steps
- Skin temperature
- All-day body-response

#### **8.10.4 SNAQ application**

During the study, the participants will document their food intake using the SNAQ App installed on a compatible iPhone/Android phone. The app will be installed and connected by the study team. The participants will be instructed to set up the CGM sensor and the SNAQ App on the phone. This instruction will either take place in person or via a phone call. After setting the CGM sensor, the Participants will be instructed to document their food intake using the SNAQ App for five days before each on-site study visit, starting during the run-in period (before visit 2), 3, and 4. This procedure is simple: the participant can introduce the data by taking a picture of the food/beverage, scanning a barcode (if available), or manually entering a particular food item into the app. This app has been used in previous clinical trials.

#### **8.10.5 Smartphones**

iPhone/Android phones compatible with the Dexcom G7, Fitbit App, and SNAQ App will be used in this study.

Study participants will be equipped with a study smartphone with pre-installed apps to connect to the wearable devices and instructed for their use. A pseudonym will be used for all created study-specific accounts.

The participant also can use her/his phone if it is compatible with Dexcom G7 and the study apps. The apps will be installed and connected by the study team.

The smartphones will only be used to synchronize the data measured with the wearable devices and SNAQ App. The synchronization will be done with the support of the study site at each study visit and will be checked by a study's member every week to guarantee the quality of the data collection. At the end of the study, the participants will return the study smartphones, physical activity trackers, and glucose-ketone meters.

#### **8.10.4 Accountability**

The study site must report the dispensing and return of the study accessories on the study accessories accountability log. Any damaged or unusable study accessory will be documented on this log. The investigator or designee must notify the Sponsor of any damaged or unusable study accessories.

The study accessories accountability log will be signed by the study coordinator of the clinical study site. This log is stored in the ISF and checked by the CRA.

Usage of the study accessories (including serial number) will be recorded in the eCRFs.

## 9. STUDY ASSESSMENTS

### 9.1 Study flow chart(s) / table of study procedures and assessments.

All visits are consigned in Table 1 (See pages 12-14).

### 9.2 Assessments of Outcomes

#### 9.2.1 Assessment of primary outcome

The primary outcome of the study is the Mean difference in 24/7 CGM percentage time spent between 3.9 and 10 mmol/L (TIR) between groups at week 16 of treatment. The primary endpoint will be evaluated by computing TIR over the 12 weeks after dose-escalation (See the treatment period in Table 1). Group A: tirzepatide+AID; Group B: SoC+AID (See Figure 1).

#### 9.2.2 Assessment of secondary (exploratory) outcomes

The secondary and exploratory outcomes will be assessed as follows:

The secondary outcomes based on CGM metrics and AID systems will be collected as described for the primary outcome and as repeated measurements from baseline to weeks 4, 8, and 16 of escalated treatment.

The anthropometric measurements and the record of the vital signs (blood pressure and heart rate, measured by pulse) will be performed according to the protocols for the World Health Organization's STEPwise approach to Surveillance (STEPS) (WHO 2017) (101). Height and body weight will be measured with *Seca Digital Ultrasonic Measuring Rod®* (Seca, Germany), with an accuracy of 0.1 kg. Waist circumference (WC) will be measured with a fiberglass anthropometric tape at the intermediate point between the lower edge of the last rib and the iliac crest in the horizontal plane (approximately 2.54 cm above the navel). The hip circumference will be measured around the widest part of the buttocks, making sure that the tape is snug but not tight, and is parallel to the floor. Body mass index (BMI) will be auto-calculated with the formula  $\text{weight}/(\text{height})^2$  in  $\text{kg}/\text{m}^2$ .

Vital sign measurements will be taken before obtaining an electrocardiogram (ECG) tracing and collecting blood samples for laboratory testing. The participant should sit quietly for five minutes before taking vital signs measurements. For each parameter, two measurements will be taken using the same arm, preferably the nondominant arm. The recordings should be taken at least one minute apart. Each pulse and blood pressure measurement will be performed sitting and recorded in the eCRF. Blood pressure will be taken with an automated blood pressure instrument.

Body composition: bioelectrical impedance analysis will assess global and regional fat mass (*Seca mBCA 514®*). For this study, fat mass percentage (FM%), fat mass index  $\text{kg}/\text{m}^2$  (FMI [total FM/height]), visceral adipose tissue liter ([I]VAT), lean mass index  $\text{kg}/\text{m}^2$  (LMI [total LM/height]) and appendicular lean mass index (ALMI [total LM/height]) will be considered relevant because they have been associated with an elevated risk of cardiometabolic diseases and mortality (102,103).

The laboratory analysis (for assessing eGFR, uACR, and lipids) will be taken according to the study schedule (See Table 1). The samples will be processed in the study site's central laboratory and reported in the International System of Units (the central laboratory reference ranges will determine the high and low laboratory limits). The HbA1c level will be measured using the DCA Vantage or a similar point-of-care device/local lab. The CKD-EPI equation will be used by the central laboratory to estimate and report eGFR(99).

MASLD will be assessed by laboratory analysis (HSI, FIB-4) and hepatic Elastography (*FibroScan®*).

The overall diabetes satisfaction will be assessed through the Diabetes Treatment Satisfaction Questionnaires. These questionnaires are for the evaluation of thoughts, concerns, and distress related to diabetes and general quality of life assessments. the status version (DTSQs) will be self-applied to the participants in a paper form at visit 2 (for the baseline) and the change version (DTSQc) at visit 4 (last visit). The provided information will be recorded in the corresponding eCRF by the study team.

#### 9.2.3 Assessment of other outcomes of interest

Patient-reported eating behavior and food intake will be assessed with the data from the SNAQ App. Participants will be instructed to document their food intake using the SNAQ App for five days before each on-site study visit, starting during the run-in period (before visit 2), 3, and 4.

## 9.2.4 Assessment of safety outcomes

### Adverse events

All adverse events and serious adverse events (SAEs) that occur during the entire duration of the study (from the time the participant signs the informed consent until the last protocol-specific procedure has been completed, including the safety follow-up period) will be documented and reported according to **Chapter 10**. The time of onset, duration, resolution, action taken, assessment of intensity, relationship to the study treatment and investigational procedures, expectedness, and seriousness will be collected and subsequently entered into the eCRF.

At the beginning of the procedure, the participants will be asked to mention any kind of discomfort. A physician will assess whether the discomfort qualifies as an adverse event. As a physician will be present during the clinical visits, the participant events will be evaluated continuously.

### Laboratory parameters

Laboratory tests are detailed in **Annex 6** and should be conducted according to the schedule of activities for each participant (**Table 1**). Any clinically significant findings from laboratory tests that result in a diagnosis and that occur after the patient receives the first dose of the investigational product should be reported by the PI/sponsor as an AE via eCRF. The samples processed and reported will be conducted as described for the secondary (and exploratory) outcomes. **See Subsection 9.4.1** for the definitions of the adverse events and when abnormal laboratory parameters will be considered adverse events.

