### Safety Outcomes

- Occurrence of clinically significant hypoglycemia and severe hypoglycemia events (see **Annex 10** for hypoglycemia classification).
- Incidence of initiation of rescue therapy for severe persistent hyperglycemia and diabetic ketoacidosis episodes.
- Incidence of gastrointestinal side effects.
- Dehydration or renal acute events.
- Adjudicated hepatic or pancreatic AEs.
- Incidence of allergic and hypersensitivity reactions.
- Mean change in heart rate from baseline to 16 weeks.
- Treatment-emergent adverse events (TEAEs).
- Early discontinuation of study drug due to AEs.

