### Vital signs

Vital signs: heartbeat by pulse and blood pressure will be assessed as described for the secondary (and exploratory outcomes). In addition, the temperature will be measured at visits 1 and 2 to rule out infection.

For each participant, a 12-lead ECG will be collected. The electrocardiograms will be recorded after the participant has been supine for five minutes in a quiet room. Electrocardiograms will initially be interpreted by a qualified physician, the investigator, or a qualified designee at the site as soon after ECG collection as possible. Ideally, when the participant is still present for immediate action, should any clinically relevant findings be identified. Any clinically significant findings from ECGs that result in a diagnosis after the participant receives the first dose of the investigational will be reported as an AE via the eCRF. Copies of ECGs collected on thermal paper should source data and be properly stored.

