## 9.2.5 Assessments in participants who prematurely stop the study.

### Individual participant-stopping criteria.

Study drug administration may be stopped for any of the following reasons:

- Three or more episodes (separated by at least 120 minutes) of clinically significant hypoglycemia (Level 2) within one day (defined as 00:00 – 23:59) of the study, after excluding other causes such as the omission of meals, unexpected increases in physical activity, or exercise (or any other contributing factor more likely than the IMP) (**See Annex 10**).
- One or more episodes of severe hypoglycemia (Level 3) (**See Annex 10**).
- One or more DKA events unrelated to the participant's AID system malfunction.
- Adjudicated hepatic or pancreatic AEs.
- Incidence of allergic and hypersensitivity reactions.
- If a participant misses three or more consecutive doses of tirzepatide due to intolerable GI symptoms (e.g., nausea, vomiting, or diarrhea) that could be reasonably attributed to the study drug, despite the mitigation plan (**See Annex 8**).
- If a participant is diagnosed with an active or untreated malignancy (other than basal or squamous cell skin cancer, in situ carcinomas of the cervix, in situ, or grade group 1 [that is, Gleason 6 or lower] prostate cancer) after randomization.
- Dehydration or renal acute events.
- Post randomization calcitonin value  $\geq 35$  ng/L and increased at least 50% over baseline.
- Supraventricular arrhythmias and cardiac conduction disorders.
- If a female participant becomes pregnant.
- Investigator decides that, in the interest of the patient, it is not medically acceptable to continue participation in the study.
- Participants with a normal BMI at baseline will be closely monitored during clinical visits. The medication will be reduced to 2.5 mg or discontinued if there is a weight gain that exceeds 5% of total body weight or if weight reduction is too rapid (defined as greater than 1% of total body weight per week) following clinical evaluation

**Table 1** describes the time points of assessment. For the definition of these AEs/SAEs and for follow-up and procedures for participants who prematurely stop the study, see **Subsection 10.1.2**.

Criteria for suspending or stopping the study.

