## 10. SAFETY

### 10.1 Drug studies

#### 10.1.1 Definition and Assessment of (Serious) Adverse Events and Other Safety-Related Events

An **Adverse Event (AE)** is any unfavorable medical event in a participant in a clinical investigation who has been administered a pharmaceutical product, and it does not necessarily have a causal relationship with the study procedure. An AE can, therefore, be any unfavorable and unintended sign (including an abnormal laboratory finding), symptom, or disease temporally associated with the use of a medicinal (investigational) product, whether related to the medicinal (investigational) product. [ICH E6 1.2]

A **Serious Adverse Event (SAE)** is classified as any untoward medical occurrence that:

- results in death,
- is life-threatening,
- requires in-patient hospitalization or prolongation of existing hospitalization,
- results in persistent or significant disability/incapacity, or
- is a congenital anomaly/birth defect.

In addition, important medical events that may not be immediately life-threatening or result in death or require hospitalization but may jeopardize the participant or may require intervention to prevent one of the other outcomes listed above should also usually be considered serious. [ICH E2A]

SAEs should be followed until resolution or stabilization. Participants with ongoing SAEs at study termination (including safety visit) will be further followed up until recovery or until stabilization of the disease after termination.

Examples of such events are intensive treatment in an emergency room or at home for allergic bronchospasm, blood dyscrasias, or convulsions that do not result in hospitalization or the development of drug dependency or drug abuse.

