#### Adjudicated hepatic or pancreatic AEs (Hepato-biliary disorders)

Hepato-biliary events will be considered AEs. All events of treatment, emergent biliary colic, cholecystitis, or other suspected events related to gallbladder disease will be evaluated, and additional diagnostic tests will be performed as needed. If a study participant experiences elevated ALT  $\geq 3X$  ULN, ALP  $\geq 2X$  ULN, or elevated TBL  $\geq 2X$ ULN, liver testing (**See Annex 9**) will be repeated within three to five days, including ALT, AST, ALP, TBL, direct bilirubin, and GGT to confirm the abnormality and to determine if it is increasing or decreasing. If the abnormality persists or worsens, clinical and laboratory monitoring will be initiated by the investigator and in consultation with the study medical monitor. ALT, AST, TBL, and ALP monitoring should continue until levels normalize or return to approximate baseline levels.

Additional safety data will be collected via the eCRF, and the IMP should be stopped if one or more of the following conditions occur:

- Elevation of serum ALT or AST  $>8$  times ULN
- Elevation ALT or AST  $>5$  times ULN for more than 2 weeks
- Elevation ALT or AST  $>3$  times ULN and TBL  $>2$  times ULN or INR  $>1.5$
- Elevation ALT or AST  $>3$  times ULN with the appearance of fatigue, nausea, vomiting, right upper-quadrant pain or tenderness, fever, rash, and/or eosinophilia ( $>5\%$ )
- Elevation ALP  $>3$  times ULN
- Elevation ALP  $>2.5$  times ULN and TBL  $>2$  times ULN
- Elevation ALP  $>2.5$  times ULN with the appearance of fatigue, nausea, vomiting, right quadrant pain or tenderness, fever, rash, and/or eosinophilia ( $>5\%$ )
- Elevated serum TBL to  $\geq 2X$  ULN (except for cases of known Gilbert's syndrome).

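### Section 9.2.4 ties laboratory and ECG adverse events to a diagnosis and a first IMP dose, against 10.1.1, so AEs may be under-counted and ascertained differently by arm

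*Protocol*

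**What the plan says.** **Laboratory and ECG rule.** Section 9.2.4 (Laboratory parameters) asks for AE reporting in the eCRF of "Any clinically significant findings from laboratory tests that result in a diagnosis", provided they arise once the participant has had a first IMP dose. The ECG paragraph under Vital signs follows the same pattern: "Any clinically significant findings from ECGs that result in a diagnosis", again after the first dose.

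**General rule.** Section 10.1.1 says an AE can be any "unfavorable and unintended sign (including an abnormal laboratory finding), symptom, or disease" temporally associated with use of a medicinal (investigational) product. It requires no diagnosis. The opening of 9.2.4 sends all AEs to Chapter 10 for documentation and reporting, and 10.1.2 collects all AEs from signed consent onwards.

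**Tie-breaker.** Section 9.2.4 refers the reader to Subsection 9.4.1 "for the definitions of the adverse events and when abnormal laboratory parameters will be considered adverse events". Section 7.4 cites the same subsection.

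**Stop rules.** Under hepato-biliary disorders, 10.1.2 says "the IMP should be stopped if one or more of the following conditions occur", followed by a list made up largely of numeric limits. Its thyroid paragraph directs discontinuation on a confirmed calcitonin value. Section 9.2.5 also gives a stop list, but in permissive terms.

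**Outcomes and analysis.** The safety outcomes in Section 5 include treatment-emergent AEs, "Early discontinuation of study drug due to AEs" and "Adjudicated hepatic or pancreatic AEs". Section 11.4.5 compares any AE/SAE between arms by chi-square test.

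**The concern.** Two passages that a site would both follow give different answers to whether a clinically significant value without a diagnosis is an AE. The liver stop rules were written to catch asymptomatic values, and those are the findings most exposed to the narrower rule. If a site codes by 9.2.4, such a finding may be absent from the AE listing, and a stop based on it may be absent from AE-related discontinuations.

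The first-dose condition adds a problem between arms. Controls have the same laboratory tests and ECGs but never receive the IMP, so on the literal wording none of their findings can become reportable under 9.2.4. The any-AE comparison would then rest on different ascertainment in the two arms of an open-label trial.

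Separately, the hepatic and pancreatic outcome is labelled as adjudicated, but the protocol describes no adjudication step, so what qualifies a case for that outcome is not fixed.

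**Working it through.** The protocol states no figure to reproduce; the check is textual.

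**1. The rules side by side**

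| Source | Diagnosis needed? | Starts at | Can a control meet it? |
|---|---|---|---|
| 9.2.4 Adverse events; 10.1.2 opening | No | Signed consent | Yes |
| 10.1.1 definition | No | No time point given | Not excluded |
| 9.2.4 Laboratory parameters | Yes | First IMP dose | No |
| 9.2.4 Vital signs (ECG) | Yes | First IMP dose | No |

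**2. The tie-breaker.** Chapter 9 ends at 9.3.8. Subsection 9.4.1 does not exist, so the references in 7.4 and 9.2.4 lead nowhere.

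**3. Stops that need no diagnosis.** The hepato-biliary list in 10.1.2 has eight conditions. Two require accompanying symptoms or eosinophilia. The other 8 − 2 = 6 are met on laboratory values alone (for example ALT or AST above 8 times ULN, or total bilirubin at or above 2 times ULN outside known Gilbert's syndrome). Of these six, two need ALP, which leaves four that rest on ALT/AST, bilirubin or INR.

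**4. Which of these the schedule can produce** (Table 1 and its notes, 9.3.4, 9.3.6, Annex 6.1)
- ALT, AST and bilirubin are measured at V3 (week 8) and V4 (week 16).
- ALP is in neither panel. After randomization it would appear only through the 10.1.2 retest or an unscheduled test.
- Calcitonin is measured after randomization only at V4, which 9.3.6 calls the end of intervention, so on scheduled tests that rule can hardly cause an early stop.
- The realistic route is therefore ALT/AST or bilirubin at week 8.

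**5. ECG stops.** The ECG-related criterion in 9.2.5 is an arrhythmia or conduction disorder. That is already a diagnosis, and 10.1.2 records it as an AE.

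**6. Direction.** The diagnosis clause can lower the AE count in the tirzepatide arm. The first-dose clause can remove findings from the control arm. The two push the between-arm difference in opposite directions, so the net direction cannot be predicted.

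**7. Scale.** With 21 participants per arm (11.2), one participant is 1/21 = 0.0476, or 4.8 percentage points. This is the weight of one case, not a forecast.

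**The case against.** A reader might infer that the diagnosis clause is the only working rule and that required drug stops will drop out of the safety outcomes. The text does not support that:

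- Section 9.2.4 opens by deferring to Chapter 10, 10.1.2 collects all AEs, and the laboratory sentence does not say *only*.
- Section 7.4 describes the missing 9.4.1 in words close to the title of 10.1.1, so the broader rule is probably the intended target.
- Section 10.1.2 says hepato-biliary events are considered AEs, and 9.2.5 refers to its stop list as AEs/SAEs.
- No ECG-triggered stop is lost.
- Calling the stops mandatory overstates 9.2.5, which says *may*.

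A reader might also infer that hepatic and pancreatic case classification is left wholly to an unblinded investigator. The pancreatitis text gives a two-of-three definition. It leaves to the investigator only the seriousness and relatedness of potential cases that do not meet all criteria. The absence of a data safety monitoring committee does not itself show that nobody adjudicates, since that is a different function.

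These points stand and narrow the consequence, but they do not remove the conflict. The 9.2.5 label cannot classify every item, because the list includes pregnancy, which Annex 7 says is not itself an AE or SAE. Section 10.1.2 leaves open whether an isolated enzyme rise is an *event*, and it never says that a raised calcitonin is an AE. None of the objections touches the first-dose condition.

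**Conclusion.** The inconsistency is real. Section 9.2.4 is narrower than 10.1.1 on diagnosis, its deciding reference is missing, and its start point cannot be met in the control arm. It may cause under-counting of AEs and different ascertainment by arm in the 11.4.5 comparison, and it may leave a week 8 liver-value stop outside AE-related discontinuations. That consequence depends on sites reading 9.2.4 literally; the documents do not show that they will, or that any stop will be missed. No rate of value-only findings is given, so the effect cannot be sized beyond 4.8 percentage points of an arm per participant, assuming all 21 are in the denominator. This is a wording defect in safety ascertainment worth correcting. It is not a flaw in the trial's design.

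**What to change.** 1. In 9.2.4, delete the diagnosis clause from the laboratory and ECG sentences. Replace the first-dose condition with a start point common to both arms, such as randomization.
2. State that any clinically significant laboratory or ECG finding, and any finding that leads to interruption or stopping of study drug, is recorded as an AE consistent with 10.1.1, together with the action taken. There is no need to make every retest threshold an automatic AE.
3. Replace the references to 9.4.1 in 7.4 and 9.2.4 with 10.1.1 and 10.1.2.
4. In Section 5 and 9.2.5, replace the adjudicated hepatic or pancreatic item with events that meet the criteria already written in 10.1.2, counted the same way in both arms.
5. Reconcile the permissive stopping language of 9.2.5 with the directive language of 10.1.2. The clinical thresholds are not at issue here and need not change for this purpose.

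The cost is amendment wording and an eCRF rule applied to results already being collected, with no new tests. The downside is a few more non-serious laboratory AEs in the listings.
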